### Data compilation and analysis

#### Data compilation

A referral form has been drawn up, to be filled in by the GP requesting inclusion in the trial of patients who fulfil the selection criteria. A data base will be designed for the electronic storage of the variables recorded in the purpose-built (physical) data record book (DRB). This database (CRDD) will be kept at the analysis centre (in the Research Support Unit, Hospital Costa del Sol, Marbella. Malaga), which will be independent of the randomisation section. Each participating centre will have a duplicate of the structure of the CRDD, together with a codebook containing the definitions and operative characteristics of all the variables. This information will be compiled within an overall file containing the data for all the variables addressed in this trial, both in the user-controlled formats and in those determined by direct observation. These data will be recorded weekly in the CRDD and sent, in coded form, to the analysis centre for safekeeping. Neither the DRB nor the CRDD will identify the group to which the patient is allocated. This information will be controlled by the physician carrying out the treatments, and who will be responsible for liaising with the randomization centre. An external assessor will record all the information except that which is reserved for the medical staff, and will manage all aspects of the distribution of the patients; nevertheless, this assessor will be blind, at all times, to the treatment actually given to each patient. Every two weeks, the analysis centre will perform a quality control exercise on the data received.

#### Monitoring data and side effects

Records will be kept of all side effects that are reported, and possible adverse events caused by the experimental treatment or the medication provided.

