There is no curative treatment for migraine, but there do exist various options for pharmacological treatment, and the choice of one type or another depends on the frequency of the attacks, their severity, the patient's activity and tolerance to side effects. In Spain it has been estimated that the most common treatment is applied at the moment of the attack (86.6%); the drugs used when a severe attack occurs include non steroidal anti-inflammatory drugs (NSAIDs) (36.7%), tryptans (28.4%), paracetamol (7.7%) and ergotamine derivatives (7.7%). Patients who suffer repeated attacks are recommended the prophylactic administration of medication such as beta blockers, tricyclic antidepressants and antiepileptic drugs [11]. The effectiveness of these treatments, although it has been corroborated by numerous studies, is limited. For severe cases, it has been estimated that one third of patients fail to respond to the administration of tryptans, which moreover are reserved for those patients who suffer the most severe attacks or who been found to respond poorly to NSAIDs. Prophylactic treatment reduces the frequency of attacks by 50%, but requires a gradual increase of the dose applied and it has an objectifiable benefit of 6 months. Prophylaxis, therefore, reduces but does not eliminate the problem and the need for medication against severe attacks [12]. Tolerance to pharmacological treatment is limited, both for therapy for severe cases and for preventive measures. The main side effects in the former case are gastrointestinal disorders (with NSAIDs) or cardiovascular problems (with ergotamine substances and tryptans). Among the side effects arising from chronic treatment are sedation, fatigue, lack of tolerance to exercise, and weight gain. In addition, there are physiological factors such as pregnancy or old age, and pathological ones such as asthma, ischemic heart disease or hypertension, for which the administration of some of these drugs is contraindicated, and this circumstance also affects the applicability of the therapy in clinical practice [12].

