Acupuncture produces complex changes in the areas of the brain concerned with pain transmission and perception, although the specific details of these effects have yet to be established. The use of neuroimaging techniques enables us to observe changes in cerebral cortical perfusion related to the type of acupuncture applied (verum or sham), and to determine the existence of specific or nonspecific patterns of cortical activation [32].

Summing up, the disparity in results obtained, depending on how the technique is applied, on the diverse therapeutic strategies possible with acupuncture, and on the need to attempt to measure the specific and the nonspecific effects of the technique, led us to design this randomised controlled pragmatic study aimed at investigating the effectiveness of acupuncture applied in primary healthcare centres for patients suffering migraine. Our goals are: a) to assess the effectiveness and safety of acupuncture in the context of standard clinical practice; b) to derive an economic evaluation of the technique; c) to determine the specific and nonspecific effects of the intervention in the study; and d) to examine changes in brain perfusion using SPECT tomography to examine the consequences of the different interventions.

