## Methods

### Design

Randomised controlled multicentre pragmatic study, with three arms, to compare the effectiveness of the individualized active acupuncture (Group A), minimal acupuncture (in locations not corresponding to acupuncture points, in different metamers and at a depth of less than 3 mm) (Group B) and conventional treatment (Group C). The patients will be blinded to the two acupuncture treatments. These patients will be assessed and the results analysed by professionals blinded with respect to the allocations of the different treatments. A stratified randomised subsample of groups A and B will be given a SPECT tomography in order to determine possible changes in the cerebral vascular flow provoked by the two different types of acupuncture applied. The duration of the study, per patient, will be 28 weeks, four of which will be prior to randomisation (baseline), followed by 8 weeks of treatment and then 16 weeks' follow up.

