### Interventions

The treatment strategies with verum and with sham acupuncture were developed by means of consensus with experienced acupuncture practitioners. All the patients will be allowed to take symptomatic medication to treat headache episodes if necessary, and to continue taking the medication to prevent migraine attacks, following their GPs' recommendations and those of the Headache Study Group of the Spanish Neurological Society [34].

The two groups will receive a total of 8 acupuncture sessions (at a rate of 1 session per week), each lasting 30 minutes, comprising the technique described below and at the locations specified. The acupuncture needles will be sterile, single-use, model S-J2030, made by Seirin Corporation (Shizuoka, Japan) in accordance with EC regulations.

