#### A) Verum acupuncture

Individualized treatment on the basis of diagnosis in accordance with traditional Chinese medicine (TCM), which the acupuncture physician may modify in accordance with the evolution of the patient's symptoms. The TCM diagnosis, evolution, points and techniques applied should be recorded in the DRB.

The doctors responsible for the treatment (specialists in acupuncture with a minimum training of 600 hours and a mean experience of 5.7 years) will insert sterile, single-use filiform acupuncture needles, with a length of 10–30 mm and a diameter of 0.20 mm, with the aid of a guide tube at each of the points, after first disinfecting the skin and with the patient in decubitus. The puncture will be made in accordance with the standards of TCM, to a depth of 1–3 cm, depending on the points selected. The insertion will be followed by stimulation performed with bidirectional rotation actions of the needle sheath in order to produce the sensation known as *Deqi*, commonly described as a sensation of irradiation. The needle will be maintained in place for 30 minutes, with 1–3 manipulations per session.

Any adverse reaction or side effect should be recorded in the DRB, with a detailed description, and stating the date of occurrence.

The time dedicated to the patients allocated to each of the groups should be identical. Similarly, the same time should be devoted to pre and post session evaluations.

The patients randomly selected for the SPECT diagnostic test will be given their first session at the Nuclear Medicine Department of the Virgen de las Nieves Hospital. The remaining sessions, as well as those applied to the other patients, will be performed at the healthcare centres participating in the trial.

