### Results measures

Each patient will fill in a headache diary during the 4 consecutive weeks immediately before the trial (baseline period), and during the 4 weeks following it (see figure 1). The diaries will be complemented with information on 4 additional weeks, from week 21 to week 24 after randomization (the follow-up period) Headache severity should be recorded in the diaries on a 3-point scale, by which 1 represents the presence of mild pain, 2 represents moderate pain and 3, severe pain (with incapacity to carry out everyday activities or necessity to remain in bed). The diary will also record the symptomatic and/or prophylactic medication taken, specifying the brand name and the number of doses. It should be clearly stated on the cover of the diary that the information contained within it is confidential. In addition, before starting the treatment, and also at 12 and 24 weeks after starting it, the patients will be requested to fill in a questionnaire with sociodemographic data and information concerning days off work because of headache; this will be compiled together with the Goldberg Anxiety-Depression Scale register and the results obtained from the Spanish version of the Headache Impact Test [36] and the SF-12 Health Survey (version 2). The purpose of this is to evaluate health-related aspects of the patient's quality of life [37]. The adverse effects of the techniques under study, and those of any rescue medication taken by the patient, will also be recorded. During the baseline evaluation, the patient will be asked to provide an anamnesis of the characteristics of the headache, in accordance with the recommendations of the International Headache Society, in order to classify the type of headache and to assess the term of the pain. Following this, an anamnesis and examination will be performed in accordance with the norms of traditional Chinese medicine.

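### Adverse-event rules depend on report or presumed cause, and contact is unequal in weeks 1–8, so safety contrasts with conventional care are open to ascertainment bias

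*Protocol article*

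**What the plan says.** The first goal listed at the end of *Background* is "to assess the effectiveness and safety of acupuncture in the context of standard clinical practice". Three sentences in the protocol article then say how harms are collected.

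- *Monitoring data and side effects* gives the general rule: "Records will be kept of all side effects that are reported, and possible adverse events caused by the experimental treatment or the medication provided".
- *Results measures*: "The adverse effects of the techniques under study, and those of any rescue medication taken by the patient, will also be recorded".
- *A) Verum acupuncture*: "Any adverse reaction or side effect should be recorded in the DRB, with a detailed description, and stating the date of occurrence". The DRB is the trial's data record book. The sham section carries the technique over unchanged apart from the *Deqi* sensation; the section on conventional treatment has no counterpart.

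On contact, *Interventions* states for A and B: "The two groups will receive a total of 8 acupuncture sessions (at a rate of 1 session per week), each lasting 30 minutes". *Design* gives the time frame after the baseline weeks: "followed by 8 weeks of treatment and then 16 weeks' follow up". For group C the article says only that the GP prescribes conventional treatment. *Interventions* lets patients in every arm continue preventive medication. All arms fill in questionnaires before treatment and at weeks 12 and 24.

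**The concern.** Two features of the stated rules combine.

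First, an event enters the record if someone volunteers it as a side effect, or if it is attributed to the needling, to rescue drugs or to medication provided. Nothing stated collects events whatever their presumed cause, and the two general rules cover different drugs.

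Second, the chance to report differs by arm during treatment. Patients in A and B meet a physician weekly for eight weeks. No comparable occasion is described for C until week 12.

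An excess of recorded events in A or B over C could then reflect opportunity to report rather than harm. In the other direction, harms of preventive drugs could be missed. *Background* lists such effects itself: "Among the side effects arising from chronic treatment are sedation, fatigue, lack of tolerance to exercise, and weight gain". They are among the harms against which the safety of acupuncture in ordinary practice would naturally be weighed.

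**Working it through.** **1. The collection rules side by side**

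| Section | Route into the record | Drugs covered |
|---|---|---|
| *Monitoring data and side effects* | reported side effects; possible events attributed to the experimental treatment or to medication | medication provided |
| *Results measures* | adverse effects of the techniques or of medication | rescue medication |
| *A) Verum acupuncture* | any reaction or side effect, entered in the DRB | not stated |

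Preventive medication is not named in any row. It is covered by the first row only if medication prescribed by the GP counts as provided, or if the patient volunteers the effect. It is outside the second row.

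**2. Recording occasions after randomisation**

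Inputs: 8 weeks of treatment (*Design*); 1 session per week in A and B (*Interventions*); questionnaires at weeks 12 and 24 in all arms (*Results measures*).

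- Sessions in A and in B: 8 weeks × 1 per week = 8, which reproduces the article's figure.
- Sessions described for C: 0.
- Diaries cover the 4 baseline weeks, weeks 9–12 and weeks 21–24, so none runs in weeks 1–8.
- Contacts in A or B: 8 + 2 = 10. Contacts in C: 0 + 2 = 2. Ratio 10 / 2 = 5.
- A against B: 10 / 10 = 1.

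The count of 2 for C is inferred from the schedule that the article describes. The instruments it lists for the shared questionnaires (sociodemographic data, days off work, the Goldberg scale, the Headache Impact Test, SF-12) include no adverse-event question.

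**3. How much could unequal contact matter?**

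The documents give no event rate and no capture probability, so this is an illustration on assumed values. Let *r* be the true risk, equal in all arms, *c* the assumed chance that an event is captured at any one contact, and *k* the number of contacts.

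Recorded rate = *r* × (1 − (1 − *c*)^*k*)

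The ratio of A or B to C is (1 − (1 − *c*)^10) / (1 − (1 − *c*)^2), so *r* cancels. With *r* = 20% assumed:

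| *c* (assumed) | A or B, *k* = 10 | C, *k* = 2 | Ratio |
|---|---|---|---|
| 0.1 | 13.0% | 3.8% | 3.4 |
| 0.3 | 19.4% | 10.2% | 1.9 |
| 0.5 | 20.0% | 15.0% | 1.3 |
| 0.8 | 20.0% | 19.2% | 1.04 |

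For scale, 270 patients allocated 1:1:1 give 90 per arm. At *c* = 0.3 the record would show about 17 patients (0.194 × 90) against 9 (0.102 × 90) with no true difference.

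The model is simple. It treats contacts as independent and lets every contact pick up every event. It also leaves out selection by attribution, which could lower the counts in A and B. It shows the direction of the effect of unequal contact and how far its size depends on *c*; it does not estimate the bias in this trial. With equal *k* in all arms the ratio is 1.0 for any *c*.

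**The case against.** The case on the other side has several good parts.

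- **The wording is broader than a pure causal filter.** The monitoring rule takes all reported side effects and merely possible adverse events, and the verum section asks for any reaction. A patient in C who volunteers an effect would be recorded. This stands: the rules do not exclude C. But a volunteered report still needs an occasion, and A and B have eight more of them.
- **Medication provided may include GP prescriptions.** That is a fair reading and would bring preventive drugs in. It would also leave the monitoring rule in disagreement with *Results measures*, which names rescue medication only. The text needs reconciling on either reading.
- **The contacts in C are inferred.** The article sets out no visit schedule for C, and the work-plan figure is not shown. The verum section asks for identical time in each group, which could be read to include C, though its link to pre- and post-session evaluations points to A and B. An external assessor, blind to treatment, also records most data. The figure of 10 v 2 is therefore a reading of the described schedule.
- **No between-arm safety test is stated.** True: no adverse-event endpoint is listed, and a description of needling reactions would serve part of the goal. The bias matters as soon as event counts in A or B are set beside those in C.
- **A condensed article leaves elicitation detail to the full protocol and record book.** Missing detail is indeed no finding. The point here is the stated rules, which select on report or cause and differ from each other.

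A reader might go further and infer that safety cannot be compared between any of the arms. The documents do not support that. A and B have the same number and length of sessions, and patients are blinded to which acupuncture they receive, so contact frequency does not distort A v B. Contrasts with C are open to bias, which is not the same as impossible. Nor does *Background* rank preventive-drug effects as the main drawback of conventional care; it lists them beside limited effectiveness, poor tolerance of acute drugs and contraindications.

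**Conclusion.** The point holds for contrasts of acupuncture, A or B, with conventional care. Under the rules as written, events are selected by report or attribution, the two general rules differ on medication, and A and B have 8 treatment-period occasions for recording where none is described for C. The expected effect of contact alone is more recorded events in A and B.

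The size is unknown. The range of 1.04 to 3.4 rests on assumed capture probabilities of 0.8 to 0.1, equal true risk and an inferred 10 v 2 contacts. If capture per contact is high, the distortion is negligible; if it is low, it is large. Because safety is a stated goal and the remedy is cheap, the change is worth making.

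**What to change.** 1. Reconcile *Results measures* with *Monitoring data and side effects*, so that one rule applies: all adverse events are recorded in all three arms whatever the presumed cause, with preventive medication explicitly included.
2. At the existing week-12 and week-24 questionnaires, have the blinded assessor put the same open question to patients in A, B and C, covering the whole interval since the last questionnaire. Placing it after the outcome instruments limits the risk that an answer mentioning needles affects their completion.
3. Use this record for any comparison with C. Report the session-by-session DRB entries separately, as a description of needling reactions in A and B.

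The cost is one added question at contacts that already exist and a short change of wording. More unrelated events will need coding, and recall over an interval of up to 12 weeks will lose some minor events. That loss should be similar across arms, which is what the comparison needs.

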#### Statistical analysis

Two types of population will be analysed: (1) population per intention to treat (ITT), with all the patients randomised; (2) population per protocol (PP), including only the patients presenting minor differences from the protocol. During analysis, the study groups will be anonymised in order to minimize biased reporting.

The baseline variables among the different groups will be compared to test the homogeneity produced by random allocation, in terms of the differences of means and proportions. The magnitude of the difference in the possible unbalancing produced by the random allocation among the groups will be evaluated using ratios of means and proportions (using that of the sham group as the reference level), and the final fit will be calculated by secondary analyses with multiple linear regression models. In the raw analysis (without fitting), significance tests will be used for the comparisons between *k *samples (parametric or not, depending on whether the distribution of the results variables is asymmetric or otherwise, and on the homogeneity of their variances), taking the control group (group C) as the reference level, and using comparison tests for the differences of the means in the main results variable (DWM1), both for the intergroup comparisons (for independent samples) and for the comparisons between the baseline and the final levels for each group (in the latter case, using tests for non-independent or paired samples).

For the main results variable (DWM1), linear regression models will be constructed, adjusted for the baseline level and analysing per ITT. The group variables will be included, taking the control group as a reference, together with the sociodemographic variables (age and sex) and the baseline variables of the severity of the complaint (pain intensity and frequency). We will adjust for possible confounders using criteria of statistical significance and of confusion. The detection of possible interactions with the treatment group variable will be evaluated by criteria of statistical significance for the corresponding interaction terms. The level of significance will be established at α < 0.05. The model will be reconstructed, removing all the observations with Cook's distances above the 90^th ^percentile of the distribution, in order to test the consistency of the results obtained.

It is our intention to perform an economic analysis from the standpoint of the Andalusia Public Health Service.

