### Randomisation and treatment allocation

Sampling will be by consecutive selection, in accordance with inclusion-exclusion criteria, over a period of 24 months until the predetermined sample size has been obtained. Randomised allocation to the three arms of the trial will be carried out using an appropriate computer program (EpiDat v 3.1), in a centralised way (by the Research Unit at Hospital Costa del Sol, Malaga), following a 1:1:1 distribution (verum acupuncture: minimal acupuncture: conventional treatment), with a sequence for each clinic in blocks of 9. Secondarily, one patient in three will be randomly selected from each of groups A and B to be given a SPECT brain perfusion study. Neither the centres nor the doctors participating in the trial will take part in the randomisation procedure, and the sequence of the latter will remain concealed until the completion of the trial. The patients who fulfil the criteria for inclusion and who give their informed consent will be included in the trial. After each patient's inclusion, his/her GP will contact the randomisation centre, where the patient will be registered, and the doctor will be told, by phone and by fax, which of the three arms of the trial the patient has been allocated to. This procedure guarantees that the randomisation process will not be influenced by the doctor participating. We shall endeavour to ensure that all participants begin the trial with the same expectations of effectiveness; accordingly, the initial information provided to the patient will state that all the treatments provided in the course of the trial are effective [13,14,16].

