### Sample size

In calculating the sample size, we assumed a power of 90% and α value of 5%, in order to detect a difference of 1.6 days with migraine with a standard deviation of 2.8 days; this implies a sample size of 72 per group in a design with three equal groups. We propose to recruit 270 patients in order to allow for a 20% withdrawal rate.

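### The days-with-migraine analysis leaves out clinic, by which randomisation is stratified, and does not fix which covariates or which analysis give the reported result

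*Protocol article*

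**What the plan says.** **Design.** Under Randomisation and treatment allocation, patients are allocated 1:1:1 "with a sequence for each clinic in blocks of 9". Study subjects gives three clinics, so allocation is stratified by clinic.

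**Analysis of DWM1.** Statistical analysis describes two layers.

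- An unadjusted comparison of the groups, parametric or not according to the observed distribution and variances. Clinic is not mentioned.
- Linear regression by intention to treat, adjusted for baseline level, with group (control as reference), age, sex, and baseline pain intensity and frequency. Clinic is not among these terms.

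Further terms depend on the data: "We will adjust for possible confounders using criteria of statistical significance and of confusion". Confusion is read here as confounding, usually judged by the change in the treatment estimate. On effect modification: "The detection of possible interactions with the treatment group variable will be evaluated by criteria of statistical significance".

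**Status of the regression.** The paragraph on baseline imbalance says that "the final fit will be calculated by secondary analyses with multiple linear regression models". The next paragraph specifies regression models for the main outcome. Neither states which analysis decides the trial.

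**The concern.** Blocking within clinic makes the arms alike in clinic mix. If outcomes differ between clinics, the true sampling variation of the group difference is smaller than an analysis ignoring clinic assumes. The design has then bought precision that the analysis does not use.

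Clinic could still enter as a possible confounder, but the stated criteria suit it badly. A factor balanced by design hardly moves the treatment estimate, so a confounding criterion tends to leave it out. A significance criterion would admit it only if the observed clinic differences happened to be large enough. Its place in the model follows from the design, not from either test.

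Separately, the selection rule has no candidate list and no threshold, and nothing says which fitted model supplies the reported effect. With the unadjusted tests alongside, the single primary endpoint can yield several estimates and p-values with no stated order among them.

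**Working it through.** **Inputs.** From Sample size: "detect a difference of 1.6 days with migraine with a standard deviation of 2.8 days", with 90% power, α of 5%, and 72 per group. Two-sided testing is assumed because sidedness is not stated. The share of outcome variance due to clinic, *s*, is not in the document, so 0 to 20% is shown. In the adjusted model *s* means the share of variance left after the other covariates.

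**The plan's own figure.** n = 2 × (1.960 + 1.282)² × 2.8² / 1.6² = 64.4, so 65 per group (66 by the t test). Dividing 66 by the rank-test efficiency of 0.955 gives 70, near the stated 72. The total follows exactly: 3 × 72 / 0.8 = 270. The sample size is not in dispute; 72 per group is used below.

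**Clinic omitted.** With 72 per arm, the standard error of a group difference ignoring clinic is 2.8 × sqrt(2/72) = 0.467, and 1.6 / 0.467 = 3.43. With arms balanced within clinic, the true standard error is 0.467 × sqrt(1 − *s*). Hence:

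- standard error too large by a factor of 1/sqrt(1 − *s*)
- actual type I error = 2 × [1 − Φ(1.96/sqrt(1 − *s*))]
- power, clinic omitted = Φ((3.43 − 1.96)/sqrt(1 − *s*))
- power, clinic included = Φ(3.43/sqrt(1 − *s*) − 1.96)

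| Clinic share *s* (assumed) | SE too large by | Type I error, omitted | Power, omitted | Power, included |
|---|---|---|---|---|
| 0% | 0% | 5.0% | 92.9% | 92.9% |
| 2% | 1.0% | 4.8% | 93.1% | 93.4% |
| 5% | 2.6% | 4.4% | 93.4% | 94.0% |
| 10% | 5.4% | 3.9% | 93.9% | 95.1% |
| 20% | 11.8% | 2.8% | 95.0% | 97.0% |

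A simulation (4,000 trials per row, 24 patients per arm in each of three clinics) agrees. At a 20% share, type I error was 2.7% with clinic omitted and 5.0% with it included; power was 94.6% against 97.0%.

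**How large these shares are.** With three equal, evenly spaced clinics, the gap from lowest to highest clinic mean is 2 × sqrt(1.5*s*) × 2.8 days: 1.0 day at 2%, 1.5 days at 5% and 3.1 days at 20%. A 5% share thus needs clinic differences about as large as the 1.6-day target effect.

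**Covariate selection.** Trials with no treatment effect and 72 per arm were simulated with five or ten candidate covariates (2,000 per setting). A covariate was kept if its p-value was below 0.05 or if it moved the estimate by more than 10%; both thresholds are assumed. Type I error was 4.6% to 5.3%. Reporting the most favourable of all 32 subsets of five covariates, which jointly explained 20% of variance, gave about 11.5% (1,000 trials).

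**Interactions.** The chance of at least one false-positive interaction among k independent tests at 5% is 1 − 0.95^k: 18.5% for four, 22.6% for five and 40.1% for ten. The number of candidates is assumed. This is not error in the DWM1 group contrast.

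**The case against.** **The clinic error is on the safe side.** Leaving clinic out makes tests conservative and costs nothing if clinic is not prognostic. The three clinics belong to one public service in one province, baseline adjustment would absorb part of any clinic difference, and power in the table stays above the planned 90% throughout. All of this stands. It limits the harm but gives no reason to ignore the stratification.

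**An article may not list every term.** The full plan might include clinic. That is possible, but the article gives the terms for its main outcome and a data-driven route for further ones. A plan that followed that text would still not guarantee clinic a place.

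**Stronger readings the text does not support.**

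- A reader might infer that the whole model is chosen from the data. The core terms are fixed in advance; only the additions are not.
- A reader might infer an inflated type I error. The 11.5% requires deliberate choice of the most favourable model, which the plan does not propose. Groups are to be anonymised during analysis, which hinders such a choice. The protection is partial: control is the regression reference and sham the reference for baseline comparisons, so using both as written could reveal the coding.
- A reader might infer that significant interactions stay in the model giving the group effect. The text says only that they are evaluated.
- A reader might see a contradiction in calling the regression secondary and then specifying it for the main outcome. A consistent reading exists: unadjusted comparison first, regression in support. The wording is ambiguous, not contradictory.

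**Conclusion.** The point holds in a limited form. As described, the analysis does not follow the stratified design. If clinic is prognostic, the cost is a somewhat oversized standard error: about 1% at a 2% clinic share, 12% at 20%, and nothing at zero. Power falls by about 2 points at most over that range (2.0 by formula, 2.4 in simulation). These sizes rest on assumed shares and on arms balanced within clinic; the upper end needs implausibly large clinic differences.

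Covariate selection under a fixed mechanical rule does not materially disturb type I error. The weakness is that no such rule is fixed and no analysis is named as decisive, so the primary endpoint lacks one predetermined result. The omission of clinic and the undeclared decisive analysis are clear from the text; the size of any harm is not. This is worth correcting before analysis, and it does not threaten the trial's validity.

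**What to change.** Name one decisive analysis of DWM1: an intention-to-treat linear regression on group, baseline days with migraine, clinic (three levels), age, sex, and the already listed baseline pain intensity and frequency. Allow no selection by significance or by change in estimate. Keep the unadjusted and rank-based tests as supporting analyses. Report any interaction tests as exploratory, in separate models, so that they cannot alter the primary contrast.

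The cost is two degrees of freedom and a change of wording. With 216 patients and one term per covariate, residual degrees of freedom go from 216 − 1 − 2 − 5 = 208 to 206. Clinic is known for every patient from the allocation sequence. Sample size and trial conduct do not change.
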